## **21 Harms**

An adverse event will be defined as any untoward medical occurrence in a subject without regard to the possibility of a causal relationship. Adverse events will be collected after the subject has provided consent and enrolled in the study. If a subject experiences an adverse event after the informed consent document is signed (entry) but the subject has not started to receive study intervention, the event will be reported as not related to study drug. All adverse events occurring after entry into the study and until hospital discharge will be recorded. An adverse event that meets the criteria for a serious adverse event (SAE) between study enrollment and hospital discharge will be reported to the local IRB [institutional review board] as an SAE.

If chemotherapy is discontinued as a result of SAE, study personnel will document the circumstances and data leading to discontinuation of treatment. A serious adverse event for this study is any untoward medical occurrence that is believed by the investigators to be causally related to study-drug and results in any of the following: Life-threatening condition (that is, immediate risk of death); severe or permanent disability, prolonged hospitalization, or a significant hazard as determined by the data safety monitoring board. Serious adverse events occurring after a subject is discontinued from the study will NOT be reported unless the investigators feels that the event may have been caused by the study drug or a protocol procedure. Investigators will determine relatedness of an event to study drug based on a temporal relationship to the study drug, as well as whether the event is unexpected or unexplained given the subject's clinical course, previous medical conditions, and concomitant medications.

The study will monitor the following adverse events during chemotherapy cycles:

Haematological

Anemia

Leucopenia

Thrombocytopenia

Febrile neutropenia

Non hematological

Nausea

Vomiting

Oral mucositis

Pain

Xerostomia

Dysphagia

Dyspnea

Anorexia

Diarrhea

Constipation

Dysgeusia

Fatigue

Peripheral Sensory neuropathy

Peripheral Motor Neuropathy

Nail infection

Weight loss

Myalgia

Joint Pain

Alopecia

Biochemical

Increase in serum creatinine

Increase in Alanine Aminotransferase (SGPT)

Increase in Alkaline Phosphatase (ALP)

Increase in Bilirubin

Decrease in serum albumin (Hypoalbuminemia)

Increase or decrease in Serum electrolytes

Sodium

Potassium

Corrected Calcium

Magnesium

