### 7.2 Secondary objective ( both stages)

1. To find out the frequency of maximum grade of toxicity (hematological and non hematological) in accordance with CTCAE (common terminology criteria for adverse events, NCI,USA) version 4.03 with the combination metronomic therapy
2. To study the evolution in serum and tissue biomarker levels during metronomic chemotherapy and their relationship to disease control
  - a. Serum angiogenic biomarkers : VEGF, VEGFR1-3, Tie-2, Angiopoietin 1-2, Thrombospondin 1, Vaso-inhibin, Angiostatin, Endostatin ,IL-8, Circulating endothelial cells and Endothelial progenitor cells,CAIX,osteopontin,
  - b. Tumor tissue marker : Thymidine phosphorylase, Hypoxia inducible factor I-alpha, DLL, SPARC , FOX-p3 Treg
3. To develop Pharmacokinetics-Pharmacodynamics (PK-PD) Model of methotrexate using CECs and serum angiogenic biomarkers as PD endpoints

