### Delivery setting

The cycles may be delivered in inpatient and/or outpatient basis. Reported adverse events, potential risks and appropriate dose modifications are described in Section 13. No investigational or commercial agents or therapies other than those described below may be administered with the intent to treat the participant's malignancy.

The starting dose of methotrexate will be 15 mg/m^2. The dose of methotrexate in a given patient will remain fixed in the subsequent cycles subject to the dose modification criteria mentioned below. Dose de escalation will be done for methotrexate only as per the schedule mentioned below. Once the clinically effective and biologically optimal dose of methotrexate is discovered then this dose will be administered in subsequent stage 2 study.

| Dose Level                                                        | Dose of Methotrexate* |
|-------------------------------------------------------------------|-----------------------|
| Level 0 – Starting Dose                                           | 15 mg/m   |
| Intermediate dose level between dose level 0 & 1
(if required) | 13 mg/m   |
| Level 1                                                           | 12 mg/m   |
| Intermediate dose level between dose level 1 & 2 (if
required) | 10 mg/m   |

|                                                                |                      |
|----------------------------------------------------------------|----------------------|
| Level 2                                                        | 09 mg/m  |
| Intermediate dose level between dose level 2 & 3 (if required) | 07 mg/m  |
| Level 3                                                        | 06 mg/m  |
| Intermediate dose level between dose level 3 & 4 (if required) | 04 mg/m  |
| Level 4                                                        | 03 mg/m  |

Table 2: Dose levels of methotrexate for dose de escalation.

| Day | Agent               | Dose                                                                                               | Route                        | Schedule      |
|-----|---------------------|----------------------------------------------------------------------------------------------------|------------------------------|---------------|

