## 27 Risks

Side effects associated with the delivery of MCT are to be expected as risks. Previous data from India has shown that this regimen is well tolerated. We anticipate that the risk of local mucositis , loose motions and skin rash side effects may be increased with the use of erlotinib with methotrexate and celecoxib. However risk of other side effects like hematological, neurological and renal side effects are unlikely to be increased.

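### Section 21 ends AE and SAE reporting at hospital discharge, contradicting the toxicity schedule, and its SAE definition requires drug causality and omits death

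*Protocol*

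**What the plan says.** Section 21 (Harms) of the protocol sets four things that matter here.

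- **Recording window for AEs.** "All adverse events occurring after entry into the study and until hospital discharge will be recorded".
- **Reporting window for SAEs.** An SAE is reportable if it occurs "between study enrollment and hospital discharge will be reported to the local IRB". After a patient is discontinued, an SAE is reported only if the investigator thinks the drug or a protocol procedure may have caused it.
- **Definition of an SAE.** It opens with a causality condition: "any untoward medical occurrence that is believed by the investigators to be causally related to study-drug and results in any of the following". Four outcomes are then listed, namely a life-threatening state, lasting or severe disability, a prolonged hospital stay, and a significant hazard, which is for the DSMB to determine. By contrast, the same section defines an AE "without regard to the possibility of a causal relationship".
- **Monitored events.** A list of haematological, non-haematological and biochemical terms to be followed during chemotherapy cycles. Rash is not on it.

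On the setting, the Delivery setting text in Section 11.2 states: "The cycles may be delivered in inpatient and/or outpatient basis". The Followup text in Section 11.2 continues treatment in 4-week cycles until progression or intolerable side effects.

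**The concern.** Hospital discharge is a natural end point for an inpatient intervention. It does not fit tablets taken for months by patients who may never be admitted. The text therefore needs a different window, and other sections of the same protocol already supply one for toxicity.

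The SAE definition raises a separate problem. Seriousness normally describes what happened to the patient, and relatedness is a judgement made afterwards. Here the judgement comes first and acts as a filter. In a single-arm trial in advanced cancer there is no control group against which to check that judgement, and Section 21 bases it partly on whether the clinical course could explain the event. Death and a new hospital admission, two of the outcomes of most interest to an oversight body, are not named.

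At stake are the SAE reports that the IRB receives and the consistency of the data behind the first secondary objective in both stages, the maximum toxicity grade (Section 7.2).

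**Working it through.** No sample size, power or error rate is involved, so the check compares the sections with one another and then follows typical events through Section 21 as written.

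**Step 1: the window.** These places describe a wider collection than Section 21 does.

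- Sections 11.1 and 12.1: toxicity by CTCAE 4.03 at day 8 of cycle 1, at day 30 and then monthly until progression.
- Section 11.4: every toxicity is to be evaluated by CTCAE 4.03.
- Section 13, Table 7: toxicity charting is ticked at day 8 of cycle 1, on day 1 of every later cycle and at progression.
- Section 16.2: toxicity is assessed at clinic visits.
- Section 17: one proforma at day 8 and another for each cycle.

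None mentions discharge. All concern toxicity charting, and none extends SAE reporting to the IRB. For AEs the protocol therefore contradicts itself. For SAEs the discharge rule stands alone.

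**Step 2: the SAE definition.** I looked for any section that adds an outcome or removes the causality condition and found none. Section 23.6 mentions death alongside SAEs, but only for compensation.

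**Step 3: events followed through Section 21 as written.**

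1. *A patient on treatment at home dies and the investigator attributes the death to the cancer.* The event is not believed drug-related, so it is not an SAE.
2. *A patient dies and the investigator suspects the drug.* Death is not a listed outcome. The event qualifies only if it is also treated as life-threatening or as a significant hazard.
3. *An outpatient is admitted for severe diarrhoea thought to be drug-related.* The list contains prolonged hospitalisation but not a new admission. Whether the event qualifies depends on how that term is read.
4. *A drug-related life-threatening event occurs at home after an earlier hospital stay.* It meets the definition, but discharge has already closed the window. If the patient was never admitted, there is no discharge date and the window is undefined.
5. *A serious bleed follows a protocol biopsy.* Section 12.2 plans three biopsies: at baseline, at day 8 and at progression. Events after consent but before the first dose are classed as unrelated to study drug, so a complication of a pre-dose biopsy can never be an SAE. At day 8 the definition still requires drug causality. The rule for discontinued patients mentions procedures, but it applies to SAEs, which are already limited to drug-related events.

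**Step 4: rash.** Three places expect it. The Risks row of Section 3 lists it among the usual effects of erlotinib. The supportive-care guidelines in Section 11.2 give measures from Grade II, so it must be graded. Section 27 states: "We anticipate that the risk of local mucositis , loose motions and skin rash side effects may be increased". The nearest terms on the Section 21 list are nail infection and alopecia.

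**Step 5: scope.** Section 15 plans 20 to 30 patients in Stage 1 and 76 in Stage 2: 20 + 76 = 96 and 30 + 76 = 106. The Section 21 rules cover all of them.

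**The case against.** The strongest reply is that toxicity is well covered elsewhere. The sections in Step 1 schedule it at clinic visits until progression, and Section 19 adds a prespecified toxicity form for each patient. Section 21 itself says that the listed events are followed during chemotherapy cycles, which last 4 weeks and repeat until progression. For a patient who is never admitted, the discharge window could also be read as open rather than empty. This stands. A reader might infer that AEs are recorded only until discharge, that toxicity will be under-counted and that the toxicity objective will be biased. The documents do not support that; they support a contradiction whose effect depends on which text staff follow.

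A second reply is that deaths and serious events have other routes to oversight. Section 2 follows Stage 2 patients until death, although the Followup text in Section 11.2 leaves follow-up after progression to institutional norms. Section 11.3 requires life-threatening complications to be notified at once to the principal investigator. Section 20.1 gives the DSMB oversight of the data, and Section 23.1 sends safety reports to the IRB every six months. So it would be wrong to infer that deaths are lost, or to size the problem by the deaths expected in this population: those are all-cause deaths, not missed toxicities. These routes soften the gap but do not close it, because none makes an unrelated or post-discharge event an SAE.

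A third reply concerns the monitored list. The toxicity form is not shown and may include rash, and Section 11.4 would let rash be recorded in any case. It cannot be said that rash will go unrecorded. Nor is neutropenia a gap of the same kind: leucopenia and febrile neutropenia are listed, and hemograms are scheduled. Rash remains a documented mismatch within the protocol.

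**Conclusion.** Section 21 is wrong as written, on three counts of unequal strength.

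- **SAE definition and reporting window: firm.** Causality is built into the definition, death and new hospitalisation are not named, protocol procedures are left out, and reporting closes at discharge. No other section repairs any of this. Serious or fatal events judged unrelated, or arising outside a hospital stay, may not reach the IRB as SAEs.
- **AE recording window: a contradiction.** Section 21 disagrees with Sections 11.1 and 12.1 and Table 7. Bias in the toxicity results is possible but not shown.
- **Rash: a mismatch** between the monitored list and three other places in the protocol.

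The number of events affected cannot be estimated from the documents. The conclusion assumes that staff apply Section 21 literally for SAE reporting and that a substantial part of treatment is taken outside hospital. The second assumption is an inference: the protocol allows outpatient delivery, and Section 11.5 checks intake by verbal report from the patient and closest caretaker, but it does not say what share is taken at home. The SAE wording alone justifies correction before enrolment.

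**What to change.** Amend Section 21 as follows.

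1. Record AEs and report SAEs from consent through treatment and progression, in line with Table 7, and for a stated interval after the last dose, whatever the care setting. The sponsor should choose and state the interval; the protocol gives none.
2. Define an SAE by outcome alone, and name death and new or prolonged hospitalisation among the outcomes.
3. Record relatedness to study drug, and to a protocol procedure, as separate fields. Reconcile the rule for events before the first dose and the rule for discontinued patients with this.
4. Add rash to the monitored list, and confirm that the toxicity form carries it.

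The cost is one amendment to Section 21, a check of the forms, and somewhat more SAE reporting, because deaths and admissions due to the cancer would now be reported and then classified. Sample size, endpoints and visit schedule through progression do not change.

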
## 22 Auditing

The trial data will be audited at 6 monthly intervals to monitor the participant enrolment, consent, eligibility, and allocation to study groups; adherence to trial interventions and policies to protect participants, including reporting of harms; and completeness, accuracy, and timeliness of data collection. An independent auditing body will be tasked with this proposed which has been identified by the data safety and monitoring body (DSMB).

## 23 Ethics and Dissemination

### 23.1 Ethics Approval

This protocol and the template informed consent forms contained in Appendix II will be reviewed and approved by the institutional IRB with respect to scientific content and compliance with applicable research and human subjects regulations. The protocol, site-specific informed consent forms (local language and English versions), participant education and recruitment materials, and other requested documents—and any subsequent modifications — also will be reviewed and approved by the IRB. Subsequent to initial review and approval, the IRB will

review the protocol at least annually. The Investigator will make safety and progress reports to the IRB at six monthly intervals and within three months of study termination or completion. These reports will include the total number of participants enrolled and summaries of each DSMB [data safety and monitoring board] review of safety and/or efficacy.

### **23.2 Protocol amendments**

Any modifications to the protocol which may impact on the conduct of the study, potential benefit of the patient or may affect patient safety, including changes of study objectives, study design, patient population, sample sizes, study procedures, or significant administrative aspects will require a formal amendment to the protocol. Any and all such amendments will be communicated to the institutional IRB for review and approval. Administrative changes of the protocol are minor corrections and/or clarifications that have no effect on the way the study is to be conducted. These may be communicated to the IRB at the investigators' discretion.

### **23.3 Consent / Assent**

Patients will be given the patient information sheet by the trial investigators / nurses. The purpose and reasons behind the study will be communicated to the patient. All patients will be provided with a copy of the written informed consent as well as the patient information sheet. Consent will be recorded on video/paper as per institutional IRB guidelines.

### **23.4 Confidentiality**

All study-related information will be stored securely at the study site. All participant information will be stored in locked file cabinets in areas with limited access. All laboratory specimens, reports, data collection, process, and administrative forms will be identified by a coded ID [identification] number only to maintain participant confidentiality. All records that contain names or other personal identifiers, such as locator forms and informed consent forms, will be stored separately from study records identified by code number. All local databases will be secured with password-protected access systems. Forms, lists, log books, appointment books, and any other listings that link participant ID numbers to other identifying information will be stored in a separate, locked file in an area with limited access.

### **23.5 Access to Data**

The Data Management Coordinating Center will oversee the intra-study data sharing process, with input from the Data Management Subcommittee. All Principal Investigators will be given

access to the cleaned data sets. Project data sets will be housed on the project specific database created for the study, and all data sets will be password protected.

### **23.6 Ancillary and post trial care**

Patients will be treated with supportive care and palliative care. In addition in the event of intolerable side effects or disease progression palliative radiotherapy may be used for their treatment. These costs will not be reimbursed for the patient as they are standard of care for such patients.. Patients will be treated for trial related adverse events in the hospital. Trial related compensation for death / SAEs will be provided as per institutional guidelines.

## **24 Dissemination Policy**

The trial results will be submitted for publication in international peer reviewed journals and presented at national/international conferences. No publication restrictions will be imposed by trial sponsors. All co investigators will be given authorship on the manuscript as well as on any abstract that are reported in national/international conferences. The principal investigators will take the roles of the corresponding author and first author positions as decided mutually. Authorship criteria for other publications stemming from the study will be decided as per the relative contributions and existing institutional guidelines. The contribution of all investigators will be acknowledged in such manuscripts if they are not eligible for authorship. In addition the grant giving organizations will also be acknowledged in all publications.

## **25 Feasibility**

On an average in TMC, 30 chemoresistant patients receive palliative chemotherapy for advanced oral cavity cancers per month. The maximum required sample size for the present study is 30 patients ( 6 x 5 dose levels). Assuming that only 10% of the eligible patients are willing to participate in this trial we expect 30 patients to be recruited within a period of 24 months from the date of start of recruitment. Hence around 70 patients ( cumulative number required for stage I/II ) would be recruited within 4 years.

## **26 Funding**

We will be seeking intramural funding from Tata memorial Centre (TMC) as well as extramural grants from agencies like, ICMR and Wellcome Trust.

## 27 Risks

Side effects associated with the delivery of MCT are to be expected as risks. Previous data from India has shown that this regimen is well tolerated. We anticipate that the risk of local mucositis , loose motions and skin rash side effects may be increased with the use of erlotinib with methotrexate and celecoxib. However risk of other side effects like hematological, neurological and renal side effects are unlikely to be increased.

